## Abstract

**Abstract:**

**Introduction:**

Selective fetal growth restriction (sFGR) in monochorionic twin pregnancy, defined as an estimated fetal weight (EFW) of one twin <10th centile and EFW discordance ≥25%, is associated with stillbirth and neurodisability for both twins. The condition poses unique management difficulties: on the one hand, continuation of the pregnancy carries a risk of death of the smaller twin, with a high risk of co-twin demise (40%) or co-twin neurological sequelae (30%). On the other, early delivery to prevent the death of the smaller twin may expose the larger twin to prematurity, with the associated risks of long-term physical, emotional and financial costs from neurodisability, such as cerebral palsy.

When there is severe and early sFGR, before viability, delivery is not an option. In this scenario, there are currently three main management options: (1) expectant management, (2) selective termination of the smaller twin and (3) placental laser photocoagulation of interconnecting vessels. These management options have never been investigated in a randomised controlled trial (RCT). The best management option is unknown, and there are many challenges for a potential RCT. These include the rarity of the condition resulting in a small number of eligible pregnancies, uncertainty about whether pregnant women will agree to participate in such a trial and whether they will agree to be randomised to expectant management or active fetal intervention, and the challenges of robust and long-term outcome measures. Therefore, the main objective of the FERN study is to assess the feasibility of conducting an RCT of active intervention vs expectant management in monochorionic twin pregnancies with early-onset (prior to 24 weeks) sFGR.

**Methods and analysis:**

The FERN study is a prospective mixed-methods feasibility study. The primary objective is to recommend whether an RCT of intervention vs expectant management of sFGR in monochorionic twin pregnancy is feasible by exploring women’s preference, clinician’s preference, current practice and equipoise and numbers of cases. To achieve this, we propose three distinct work packages (WPs). WP1: A Prospective UK Multicentre Study, WP2A: a Qualitative Study Exploring Parents’ and Clinicians’ Views and WP3: a Consensus Development to Determine Feasibility of a Trial. Eligible pregnancies will be recruited to WP1 and WP2, which will run concurrently. The results of these two WPs will be used in WP3 to develop consensus on a future definitive study. The duration of the study will be 53 months, composed of 10 months of setup, 39 months of recruitment, 42 months of data collection, and 5 months of data analysis, report writing and recommendations. The pragmatic sample size for WP1 is 100 monochorionic twin pregnancies with sFGR. For WP2, interviews will be conducted until data saturation and sample variance are achieved, that is, when no new major themes are being discovered. Based on previous similar pilot studies, this is anticipated to be approximately 15–25 interviews in both the parent and clinician groups. Engagement of at least 50 UK clinicians is planned for WP3.

**Ethics and dissemination:**

This study has received ethical approval from the Health Research Authority (HRA) South West—Cornwall and Plymouth Ethics Committee (REC reference 20/SW/0156, IRAS ID 286337). All participating sites will undergo site-specific approvals for assessment of capacity and capability by the HRA. The results of this study will be published in peer-reviewed journals and presented at national and international conferences. The results from the FERN project will be used to inform future studies.

**Trial registration number:**

This study is included in the ISRCTN Registry (ISRCTN16879394) and the NIHR Central Portfolio Management System (CPMS), CRN: Reproductive Health and Childbirth Specialty (UKCRN reference 47201).

STRENGTHS AND LIMITATIONS OF THIS STUDYThe research question—acceptability and feasibility of this proposed trial has not been investigated previously.Uses a mixed-methods design incorporating prospective multicentre, qualitative and consensus-building approaches to enhance methodological robustness and rigorous multifaceted investigation.Includes a prospective UK multicentre study (work package 1) that systematically gathers data across various centres to ensure diverse input and data richness.Employs qualitative interviews to deepen understanding of participant and clinician perspectives, enriching the data’s contextual validity.Given the rarity of the condition under study, the study may face challenges in achieving sufficient power to fully explore certain perinatal outcomes.

## Introduction

 Twin pregnancy is associated with an increased risk of adverse fetal and neonatal outcomes, such as stillbirth and neonatal death compared with singletons.^1^ Twin pregnancies are also at fourfold increased risk of neurological sequelae such as cerebral palsy compared with singletons.^2^ Monochorionic (MC) twin pregnancies, where both fetuses originate from the same conception and share one placenta, represent 25%–30% of all twin pregnancies.^3^ MC twin pregnancies pose unique difficulties for management because of complications from a shared placenta and communication between the fetal circulations. These can lead to the two common pathologies seen in MC twin pregnancies: twin-to-twin transfusion syndrome (TTTS) and selective fetal growth restriction (sFGR). sFGR, when one fetus grows normally while the other is growth restricted, affects approximately 10%–15% of MC twin pregnancies.

Definitions of sFGR in MC twin pregnancy vary, but current UK guidelines define sFGR as an intertwin estimated fetal weight (EFW) discordance of >20% after 20 weeks.^3 4^ The ISUOG (International Society of Ultrasound in Obstetrics and Gynecology) guideline supports using the smaller twin being <10th centile and an intertwin discordance of ≥25%0.^5^ Early-onset sFGR, occurring prior to 24 weeks’ gestation, is less common but is associated with greater risk to the fetus and poses substantial management difficulties due to the distance from viability.^6^ sFGR in MC twin pregnancy is conventionally classified into three subtypes based on the umbilical artery (UA) Doppler (figure 1) according to Gratacós *et al*: type I (positive end-diastolic flow (EDF) in the UA) has the best outcome, type II (persistent absent/reversed EDF) the worst prognosis and type III (intermittently absent/reversed EDF) has an unpredictable course.^7^

**Figure 1 F1:**
[figure not shown]
Classification of selective fetal growth restriction according to umbilical artery flow patterns.

There are three main management options for sFGR:

(1) Expectant management: close monitoring until the decision for timed birth is made. This carries a risk of intrauterine demise (IUD) of the smaller twin, which may result in co-twin demise (40%) or neurological sequelae (30%), thought to be secondary to hypotension in the larger twin due to intertwin transfusion via placental vascular connections.^3^ (2) Selective termination by bipolar cord coagulation (BCC) or radiofrequency ablation (RFA). This may protect the larger baby from harm if the smaller twin were to subsequently die. However, termination may not be acceptable to some parents. (3) Placental laser photocoagulation of connecting vessels to protect the larger twin in the event of death of the smaller twin. This is often technically challenging and may worsen the outcomes of the smaller twin.^8^,^11^ Active intervention options include selective termination through either BCC or RFA, as well as placental laser photocoagulation of connecting vessels.

We conducted a preliminary survey of 29 UK fetal medicine clinicians to establish their current practice for the management of sFGR in MC twin pregnancies.^12^ Our survey revealed significant variation in diagnostic criteria, management and surveillance protocols for the three different types of early-onset sFGR in MCDA (Monochorionic diamniotic) twin.^12^ Great uncertainty also remains over what interventions, if any, women would be willing to accept at different gestations. The current paucity of qualitative data and patient experience information may hamper a subsequent clinical trial.^12^ The loss of a fetus is associated with long-term psychological effects for the parents.^13^ Furthermore, the lifelong cost of prematurity-associated neurodisability, such as cerebral palsy, may be substantial.^14^,^18^

Therefore, there is a lack of consensus on the optimal management (expectant or intervention) of sFGR in MC twin pregnancies and the most appropriate timing of delivery. Each management option carries risks and benefits in terms of the key outcomes of stillbirth and cerebral palsy; what is currently unknown is the relative risk–benefit ratio for each option.

No randomised controlled trials (RCT) or Cochrane reviews have investigated sFGR. Until recently, published systematic reviews^9 11^ assessed mortality and morbidity, especially cerebral injury,^18^ but did not compare outcomes based on management. We have published a meta-analysis of the perinatal mortality and morbidity in sFGR according to management^8^ which demonstrated significant bias in the published literature. Studies were retrospective and non-randomised, with significant heterogeneity in included populations, management and outcomes.^8^ This meta-analysis was, therefore, unable to explore the association between gestational age at delivery and neonatal outcomes. This is fundamental as gestational age at delivery is the main determinant of perinatal outcome in twins.^17 18^ Primary research has not identified a significant difference between RFA and BCC for selective fetal reduction for sFGR in MC twin pregnancy.^19 20^ In summary, to quote the Royal College of Obstetricians and Gynaecologists,^3^ ‘Due to a lack of available high-quality evidence, there is no clear guidance on how to manage sFGR in such pregnancies.’

The primary objective is to recommend whether an RCT of intervention versus expectant management of sFGR in MC twin pregnancy is feasible by exploring women’s preference, clinician’s preference, current practice and equipoise and numbers of cases.

## Methods and analysis

### Study design

FERN is a mixed-methods feasibility study with three distinct work packages (WPs) to determine the overall research objectives (figure 2).

**Figure 2 F2:**
[figure not shown]
FERN study flow chart.

### WP 1: a prospective UK multicentre study

We will conduct a prospective UK multicentre study to determine the incidence, natural history and outcomes of MCDA twin pregnancies complicated by sFGR according to whether they had expectant management or fetal intervention.

The data will provide the following key outcomes:

Proportion of women who opt for expectant management, active fetal intervention or termination of the entire pregnancy. We will have reasonable precision of these estimates from current routine practice, which is critical for any future research including an RCT.We will learn about management of these pregnancies, that is, frequency of monitoring, timing of delivery, thresholds for intervention.Incidence of adverse outcomes. However, some subgroups may be small so the precision of some estimates might be inaccurate, with wide 95% CIs. We will use the data from the UK twin registry to ascertain the accuracy of these estimates.

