#### Eligibility criteria

Women with an MCDA twin pregnancy and a diagnosis of sFGR (EFW of one twin <10th centile+EFW discordance ≥25%) and gestational age at diagnosis between 16^+0^ and 23^+6^ weeks based on ultrasound and who can provide informed consent will be considered eligible for WP1. The exclusion criteria include higher order multiple pregnancies, maternal age under 18 years, other MC complications (such as TTTS or twin anaemia polycythaemia sequence before enrolment), other rare complicated MC twin pregnancies at enrolment (such as twin reversed arterial perfusion syndrome, known karyotype abnormality, known major fetal structural abnormality defined as a lethal, incurable or curable severe abnormality with a high risk of residual disability), an indication for immediate delivery, preterm prelabour rupture of membranes before enrolment. In addition, women who lack the capacity to give informed consent or suffer from any medical or psychiatric condition which compromises their ability to participate will also be excluded.

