#### Recruitment and sampling

We will approach all women with sFGR as defined by the eligibility criteria. Further to two no-cost extensions granted by the NIHR due to delayed setup and recruitment and rarity of the condition under study, there will be a 42-month data collection period (39-month recruitment) from 22 UK sites, (compared with the originally proposed 18-month data collection period). The planned start and end dates for the study are 1 July 2021 and 30 November 2025, respectively. Our recent survey suggests that we should be able to recruit two women per month per centre; if we assume a conservative 40% recruitment rate, our pragmatic estimate is that we will recruit over 100 women in the study period. All participants will be recruited from their local fetal medicine or antenatal clinic. They will be contacted in person by a member of the clinical research team (principal investigator (PI)/research midwife/delegated authority) and invited to take part in the study. Potential participants will be given written and verbal information on the FERN study and provided with the opportunity to ask questions and take any additional time required to consider taking part in the study. Following this, participants will be asked to sign the study-specific informed consent form in the presence of the site researcher. Once eligibility has been confirmed by the PI at the site, and informed consent has been obtained, the participant will be registered and then entered into the study using a bespoke electronic data capture system that will generate a unique participant identification number. The data will be collected on a range of data items described on the FERN REDCap database. The follow-up will continue until of discharge of baby/babies from the hospital/neonatal unit. This database is designed and maintained by the University of Liverpool, IT Services in collaboration with the chief investigator and research manager. The eCRF (electronic case record form) is the primary data collection instrument for the study. All data requested on the eCRF must be recorded and all missing data explained. WP1 is a prospective observational study, therefore, all data will be collected prospectively by trained members of the research team at each study site.

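### WP1 enters only consenting women and names no MCDA denominator, so as described it cannot determine sFGR incidence or case numbers, and its management proportions apply to consenters rather than to routine practice

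*Protocol article*

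**What the plan says.** The article's section on WP 1 gives the purpose of this work package as "to determine the incidence, natural history and outcomes of MCDA twin pregnancies complicated by sFGR", with results set out by the management received. The first listed output is "Proportion of women who opt for expectant management, active fetal intervention or termination of the entire pregnancy". Of this the section says: "We will have reasonable precision of these estimates from current routine practice, which is critical for any future research including an RCT". The third output is how often adverse outcomes occur. A caution about wide intervals in small subgroups follows, and then "We will use the data from the UK twin registry to ascertain the accuracy of these estimates".

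The data source is fixed under WP 1, Recruitment and sampling. The intention is stated as "We will approach all women with sFGR as defined by the eligibility criteria", but data begin only once "informed consent has been obtained, the participant will be registered and then entered into the study". Under WP 1, Eligibility criteria, women "who can provide informed consent will be considered eligible for WP1"; that concerns ability to consent, not the decision to do so.

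The primary objective, at the end of the Introduction, includes women's preference, current practice and the number of cases. Statistical/data analysis considerations promises a 95% CI with every statistic.

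**The concern.** The stated targets and the stated sampling frame do not match.

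Incidence needs every case in the numerator and every MCDA pregnancy under observation in the denominator. A consented case series leaves non-participants out of the first and does not supply the second. The number of eligible cases fails for the same reason.

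The management proportions have a denominator, but it is women who agreed to be followed. The article presents them as estimates from routine practice and calls them critical for a later RCT. If willingness to join is related to the management chosen, they are shifted. The 95% CI gives no warning of this, because it measures sampling error only.

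At stake is the feasibility decision. Case numbers and current practice are named in the primary objective, and both bear on how many women an RCT could approach.

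**Working it through.** **1. Frame against target**

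- sFGR incidence: needs all cases and all MCDA pregnancies observed. The article supplies consenting cases and no denominator.
- Number of eligible cases: needs all eligible women. The article supplies those registered.
- Management proportions: need the management chosen by all eligible women. The article supplies it for those registered.

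**2. The article's own recruitment figure**

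Inputs from WP 1, Recruitment and sampling: 22 sites, two women per month per centre, 39 months, 40% recruitment rate.

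- 22 × 2 × 39 = 1,716, and 1,716 × 0.40 = 686.
- The stated expectation is about 100 (or over 100). The inputs do not reproduce it; 686 meets it only as an inequality.

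This mismatch is a separate matter. It is relevant here because it shows that the 40% does not drive the sample size, so its meaning is uncertain. It may be a consent fraction, or a discount on hoped-for recruitment. Below, 40% as uptake is an assumption.

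**3. Bias in a management proportion**

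Let u be uptake, P1 the proportion among participants and P0 that among eligible non-participants.

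- All eligible women: u·P1 + (1 − u)·P0
- Bias of the participant estimate: P1 − [u·P1 + (1 − u)·P0] = (1 − u)(P1 − P0)

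With u = 0.40 the bias is 0.6 × (P1 − P0). A 10-point difference gives 6 points and a 20-point difference gives 12. No difference gives zero.

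**4. Comparison with the reported precision**

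- Largest 95% half-width at n = 100: 1.96 × √(0.25/100) = 9.8 points.
- Difference at which bias equals it, with u = 0.40: 9.8/0.6 = 16.3 points.

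Because the 40% is ambiguous, the same threshold at other assumed uptakes:

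- u = 0.058 (100/1,716, if the survey rate were right): 9.8/0.942 = 10.4 points
- u = 0.20: 9.8/0.80 = 12.3 points
- u = 0.60: 9.8/0.40 = 24.5 points
- u = 0.80: 9.8/0.20 = 49 points

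**5. Direction**

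Assume a true intervention share of 30% (the documents give none), and let women choosing intervention consent r times as often as the others. The observed share is 0.3r/(0.3r + 0.7).

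- r = 0.5: 0.15/0.85 = 17.6%
- r = 1: 30%
- r = 2: 0.60/1.30 = 46.2%

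The shift can go either way, and the article gives no value for r.

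**6. Logical limits**

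For an observed 30/100 the Wilson 95% CI is 21.9% to 39.6%. With u = 0.40 and nothing known about non-participants, the value for all eligible women lies between 0.4 × 0.3 = 12% and 0.4 × 0.3 + 0.6 = 72%. These are extremes, in which no non-participant or every non-participant chose intervention. They are not an estimate of error.

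**The case against.** **The sentence on incidence may only be loosely worded.** It goes on to split results by management, which population incidence of sFGR cannot be, and the list of outputs names incidence only for adverse outcomes. This is a fair reading. But as written, incidence attaches to affected pregnancies, and case numbers are in the primary objective on any reading. At the least the wording must be settled.

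**There is an external check.** The UK twin registry is named, and by its position it serves adverse outcomes. For those, the objection has weight. Nothing says the registry covers sFGR incidence or management choice.

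**A screening log may exist.** All eligible women are approached, and Sample size calculation judges success by ability to recruit and retain, so a log is likely and may sit in the full protocol. Its absence from an article is not a fault. The article does, however, tie these estimates to WP1 data, and a bare log would hold neither the management chosen nor the MCDA pregnancies scanned.

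**WP1 is not the only source, and an RCT also enrols only consenters.** WP2 invites women whether or not they join WP1, and WP3 surveys clinicians. These inform acceptability and opinion but do not count cases or choices. Consent to observation is not consent to randomisation, and accrual planning starts from the eligible number.

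**Stronger readings a reader might infer, which the documents do not support.** One is that the proportions overstate expectant management; the direction is unknown. Another is that losses, terminations or procedures between diagnosis and enrolment are excluded by rule. The enrolment-timed exclusions cover other monochorionic complications, other rare complicated pregnancies and membrane rupture, not those events. A third is that cases are undercounted 2.5-fold (1/0.4), which needs the 40% to be a consent fraction.

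**Conclusion.** The point holds in a limited form. As the article describes it, WP1 cannot determine sFGR incidence or the number of eligible cases. This is structural: it follows from consent-only entry and the missing MCDA denominator, and it stands at any uptake below 100%.

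For the management proportions the fault is one of labelling and of an unchecked risk. They are valid for consenting women, and they describe routine practice only if consent is unrelated to management choice. The article neither shows this nor arranges to test it. With uptake assumed at 40%, it takes a participant/non-participant difference of about 16 points for the bias to match the largest sampling half-width at n = 100. Smaller differences do less, and none does nothing.

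It would go too far to say that the proportions are wrong for the eligible population, because the documents establish no difference between those who join and those who do not. The matter is worth correcting because these estimates feed the feasibility decision.

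**What to change.** Define the target as all eligible women seen at open sites during recruitment. From each site collect anonymised aggregate counts of:

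- eligible women, by management chosen and consent status;
- MCDA pregnancies scanned in the eligible window (16+0 to 23+6 weeks), from the same sites and period.

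Base case numbers, sFGR incidence and the management proportions on these counts, and compare management between participants and non-participants. Keep the consented cohort for detailed management and outcomes.

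If the counts cannot be obtained, delete the claim to determine the incidence of sFGR, label the proportions as among consenting women, and state that the 95% CIs do not cover selection by consent.

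The cost is a small site workload for the counts. The fallback is a change of wording only.

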#### Eligibility criteria

Women with an MCDA twin pregnancy and a diagnosis of sFGR (EFW of one twin <10th centile+EFW discordance ≥25%) and gestational age at diagnosis between 16^+0^ and 23^+6^ weeks based on ultrasound and who can provide informed consent will be considered eligible for WP1. The exclusion criteria include higher order multiple pregnancies, maternal age under 18 years, other MC complications (such as TTTS or twin anaemia polycythaemia sequence before enrolment), other rare complicated MC twin pregnancies at enrolment (such as twin reversed arterial perfusion syndrome, known karyotype abnormality, known major fetal structural abnormality defined as a lethal, incurable or curable severe abnormality with a high risk of residual disability), an indication for immediate delivery, preterm prelabour rupture of membranes before enrolment. In addition, women who lack the capacity to give informed consent or suffer from any medical or psychiatric condition which compromises their ability to participate will also be excluded.

